## Abstract

**Background:** While low sodium intake (<2.3g/day) is recommended for all, there is uncertainty about feasibility and net cardiovascular effects. In COSTICK, we evaluated the effects of a dietary counselling intervention (reduced sodium intake) on intermediate cardiorenal outcomes in patients with (STICK) and without (COSIP) mild/moderate kidney disease.

**Methods:** This is a protocol for two phase IIb randomised, two-group, parallel, open-label, controlled, single centre trials. Participants were aged >40 years with stable blood pressure, unchanged anti-hypertensive medications, willing to modify diet and provided written informed consent. Participants were excluded for abnormal sodium handling, heart failure, high dose diuretics, immunosuppression, pregnancy/lactation, postural hypotension, cognitive impairment, high or low body mass index (BMI) or inclusion in another trial. STICK participants had estimated glomerular filtration rate (eGFR) 30-60ml/min/1.73m
^2^ and were excluded for acute kidney Injury, rapidly declining eGFR; known glomerular disease or current use of non-steroidal anti-inflammatory drugs. For COSIP, participants were excluded for known kidney or cardiovascular disease. Participants were randomized to usual care only (healthy eating) or an additional sodium lowering intervention (target <100mmol/day) through specific counseling (sodium use in foods, fresh over processed foods, sodium content of foods and eating outside of home). In STICK the primary outcome is change in 24-hour urinary creatinine clearance. In COSIP, the primary outcome is change in five biomarkers (renin, aldosterone, high sensitivity troponin T, pro-B-type natriuretic peptide and C-reactive protein). Our primary report (COSTICK), reports six biomarker outcome measures in the entire population at 2 years follow-up.

**Discussion:**
These Phase II trials will explore uncertainty about low sodium intake and cardiovascular and kidney biomarkers, and help determine the feasibility of low sodium intake. Trial results will also provide preliminary information to guide a future definitive clinical trial, if indicated.

**Trial registration: **STICK: ClinicalTrials.gov
NCT02738736 (04/04/2016); COSIP: ClinicalTrials.gov
NCT02458248 (15/05/2016)

## Introduction

Effective, simple, inexpensive interventions are essential for population-based strategies to impact blood pressure (BP), which may impact the global burden of cardiovascular disease (CVD) and chronic kidney disease (CKD)
^
1
^. Low sodium intake (<2.3g/day) is recommended for adults
^
2
^, with specific emphasis on individuals with hypertension, CVD and CKD. In populations with hypertension (or pre-hypertension) the evidence supporting low sodium intake (compared to moderate intake, 2.3–4.6g/day) is based on Phase II trials reporting a reduction in BP
^
3–
6
^.

Meta-analyses of observational studies estimate a mean BP reduction of 10/5mmHg per 2.3g (100mmol) reduction in daily sodium intake
^
7
^ and meta-analysis of clinical trials estimate that reducing from moderate to low sodium intake reduced BP by 5.0/2.7mmHg
^
8
^. It is assumed that all BP reductions will translate into reductions in CVD and CKD progression. However, there is also evidence of activation of the renin-angiotensin-aldosterone system (RAAS) with low sodium intake in the short-term
^
9
^ and with persistent effects
^
10,
11
^ (e.g. Yanomami tribes in northwestern Brazil), and prospective cohort studies report a J-shaped association of sodium intake with cardiovascular health
^
1,
12
^. There have also been inconsistent reports about the association between sodium intake and biomarkers, including inflammatory biomarkers (C-reactive protein (CRP) and interleukin 6 (IL-6)), markers of cardiac injury/strain (high sensitivity troponin T (hsTnT) and pro B-type natriuretic peptide (proBNP) and of salt sensitivity (uromodulin)
^
13–
16
^.

For patients with CKD, no moderate or large-scale clinical trials have evaluated the effect of sustained low sodium intake on renal outcomes. Our systematic review of the association between dietary sodium intake/excretion and renal function showed that there is evidence of an association between high sodium intake, but not moderate intake, and glomerular filtration rate (GFR) decline among participants with CKD
^
17
^. Subsequent, analyses of additional observational studies reported no association between urinary sodium excretion and renal outcomes
^
18–
20
^. A prospective cohort study from Korea reported a U-shaped association between sodium intake and CKD incidence
^
21
^. A further meta-analysis of clinical trials of dietary sodium reduction in CKD included 11 trials (n=738) and reported that moderate sodium restriction reduced blood pressure and urinary protein excretion
^
22
^.

These competing observations have cast considerable uncertainty about the optimal level of sodium intake, reflected in differences in guidelines and recommendations
^
23
^. Therefore, the sustained effects of long-term low-sodium intake on biomarkers of cardiovascular and kidney function is a critical next step, necessary to inform the conduct of future definitive randomized controlled trials. 

## Protocol

### Study aim and design

Both trials were designed to explore the effects of an educational intervention to reduce sodium intake targeting low levels, compared to usual care. The
Sodium In
Take
In
Chronic
Kidney
Disease (STICK) clinical trial was designed to explore the effect of the intervention in adults with non-severe CKD on decline in renal function over two years. The
Clarifying
Optimal
Sodium
Intake in
Populations (COSIP) clinical trial was designed to explore the effect of the intervention in adults without cardiovascular disease on a panel of cardiovascular biomarkers, over two years.

Both trials are Phase IIb randomised, two-group, parallel, open-label, controlled trials conducted at a single-centre. Blinding of participants and the research dietitian was not possible for practical reasons. Participants were recruited from hospital-based outpatient clinics or attending general practitioners in the catchment area of a tertiary referral hospital in Galway, Ireland. Potentially eligible participants were invited to participate and provided written informed consent before entering a screening period, consisting of an abbreviated food frequency questionnaire (FFQ; see extended data
^
24
^), medical history, laboratory investigations, baseline physical measurements (height, weight, body mass index (BMI), hip and waist circumference) and blood pressure (BP). Office BP was measured using a calibrated, automated oscillometric device and followed by a 24-hour ambulatory blood pressure monitor (ABPM) using the Spacelabs ABP 90217 device, where BP was measured every 30 minutes between 7am and 10pm, and every 60 minutes between 10pm and 7am. Given the complementary nature of both trials, participants were screened for both trials simultaneously, but only deemed eligible and randomized into STICK or COSIP. Rescreening of participants who failed the screening visit due to a blood pressure result or medication change was permitted after a minimum of three months.

### Eligibility criteria for both trials

Inclusion criteria for both trials included age >40 years, stable blood pressure, unchanged anti-hypertensive medications, willingness to modify dietary intake and written informed consent (
Table 1). Initially, we also required dietary assessed sodium intake of >2.3g/day, but removed this after the Vanguard phase due to weak correlation between the dietary sodium assessment and baseline 24 hour urine sodium collection. Exclusion criteria for both trials included abnormal sodium handling, heart failure, high dose diuretic use, immunosuppressive medication use, unable to comply with intervention or study visits, pregnancy or lactation, postural hypotension, cognitive impairment, high or low BMI or inclusion in another clinical trial.

**Table 1. T1:** Eligibility Criteria.

	STICK	COSIP
**Inclusion Criteria**		
Age ≥40 years	✓	✓
Average Office BP<160/95mmHg	✓	✓
24hour average from ABPM<150/90mmHg	✓	✓
Anti-hypertensive and/or diuretic medications unchanged for three months	✓	✓
Self-reported willingness to modify dietary intake over sustained period	✓	✓
Written informed consent	✓	✓
Sodium Intake>2.3g/day from FFQ **	✓	✓
Most recent eGFR within 3 months	✓	✗
eGFR 30–60/min/1.73m ^2^ on ≥2 occasions ≥3 months apart	✓	✗

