**Exclusion Criteria**		
Abnormal Sodium Handling (Bartter syndrome, syndrome of inappropriate antidiuretic hormone (SIADH) secretion, diabetes insipidus or hyponatraemia (serum sodium <125mmol/L)	✓	✓
Heart Failure (New York Heart Association (NYHA) Class III or IV symptoms or known left ventricular ejection fraction 30%)	✓	✓
Total daily diuretic therapy dose exceeding frusemide 80mg, bumetanide 2mg, hydrochlorothiazide 50mg, bendroflumethiazide 2.5mg, indapamide 2.5mg, metolazone 2.5mg or the use of both a loop and thiazide diuretic)	✓	✓
Use (within one month) of tacrolimus, cyclosporine, azathioprine or mycophenolate mofetil	✓	✓
Unable to follow educational advice	✓	✓
Prescribed high-salt diet, low-salt diet or sodium bicarbonate	✓	✓
Pregnancy or lactation	✓	✓
Unlikely to comply with study procedures or follow-up visits	✓	✓
Symptomatic or treated postural hypotension	✓	✓
Known dementia or cognitive impairment	✓	✓
BMI<20 or >40kg/m ^2^	✓	✓
Participating in another clinical trial or previous study allocation	✓	✓
Acute Kidney Injury (AKI) (doubling of baseline serum creatinine within 3 months) or Rapidly declining eGFR (≥10ml/ min/1.73m ^2^) over 6 months	✓	✗
Known Kidney Disease (Post-infectious glomerulonephritis, IgA nephropathy, thin basement membrane disease, Henoch-Schonlein purpura, proliferative glomerulonephritis, membranous nephropathy (including lupus), rapidly progressive glomerulonephritis, minimal change disease or focal segmental glomerulosclerosis) or dialysis or renal transplant (prior, current or planned))	✓	✗
NSAID use for >=3 days per week (excluding aspirin <100mg/day)	✓	✗
Known CKD or most recent eGFR≤60/min/1.73m ^2^	✗	✓
Previous Cardiovascular Disease (Myocardial infarction, percutaneous coronary intervention, coronary artery bypass grafting or stroke)	✗	✓

BP=Blood Pressure; ABPM=Ambulatory Blood Pressure Monitor; FFQ=Food Frequency Questionnaire; eGFR=estimated Glomerular Filtration Rate; BMI=Body Mass Index; NSAID=non-steroidal anti-inflammatory drug; CKD=chronic kidney disease **Sodium Intake removed from Inclusion Criteria during trial due to weak correlation between dietary sodium assessment and baseline 24hour urine sodium collection

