### Randomisation

Once confirmed eligible, participant details were entered into a trial-specific, secure, web-based randomisation service. In STICK, we used a minimization strategy (including previous attendance at a dietitian, diabetes, hypertension and strata of eGFR [30–39, 40–49 and 50–60ml/min/1.73m
^2^]) to support computer-generated block randomization with 1:1 assignment to intervention or usual care. In COSIP, we used computer-generated block randomization to 1:1 assign participants to intervention or usual care. Variable block sizes were used to minimize the occurrence of chance imbalances and to preserve allocation concealment. After confirmation of eligibility, participants may have been randomised in advance to facilitate the scheduling of individuals to attend distinct clinics for either the intervention or usual care arms.

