### Study outcomes

In STICK, the primary outcome measure is change in 24-hour urinary creatinine clearance over two years. We adopt this approach, rather than eGFR, to improve reliability and validity of the primary outcome measure. In COSIP, the primary outcome measure is change in cardiovascular biomarkers (renin, aldosterone, hsTnT, proBNP and CRP) over two years. For COSTICK, the primary outcome measures are creatinine clearance, renin, aldosterone, hsTnT, proBNP and CRP. Secondary outcomes included change in (i) 24 hour ABPM, (ii) 24 hour urine sodium excretion, (iii) 24 hour urine protein, (iv) Modification of Diet in Renal Disease (MDRD) eGFR
^
25
^, (v) Chronic Kidney Disease Epidemiology Collaboration (CKD-EPI) eGFR
^
31
^, (vi) Kidney Disease Improving Global Outcomes (KDIGO) CKD risk category
^
32
^ and (vii) change in PAXgene RNA, and number of (viii) cardiovascular events (acute coronary syndrome, myocardial infarction, heart failure or stroke), (ix) syncope events (prescyncope, syncope, hypotension or orthostatic hypotension) and (x) renal events (acute kidney injury, dialysis, transplant or end stage renal disease).

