### Statistical analysis plan

Descriptive statistics will be used to describe baseline characteristics, the flow of trial participants and the amount of missing data for predictor and outcome variables. All losses to follow-up and dropouts will be accounted for and reasons documented. Participants randomised but who did not attend the randomisation visit will be included in analyses. Suitable transformations will be used if the underlying normality assumption is a concern and the bootstrap procedure and a comparison of the median change will be used if a suitable transformation cannot be made. All tests of significance will be two-sided using an alpha of 0.05 for statistical significance and will not be adjusted for multiple testing due to the exploratory nature of the trials. The primary analysis will use the intention-to-treat dataset for all outcomes. A secondary per-protocol analysis will also be carried out, with post randomisation exclusions due to ineligibility, non-compliance, loss to follow-up or missing data.

The primary analysis will consist of fitting a separate linear, multivariable analysis to each of the six outcomes: renin, aldosterone, creatinine clearance, pro-BNP, troponin, and CRP, and secondary outcome measure of 24-hour ABPM. We will review data for implausible values and exclude extreme changes (e.g. change in renin or aldosterone impacted by change in medications). Corresponding baseline measurements of each biomarker will be included as covariates in the model, along with a factor variable for the sub-study in which each patient was recruited, age, sex and whether the participant had attended a dietitian in the 6 months previous to baseline (incident vs prevalent participant). To ensure estimates are more robust to potential effects of missing data at 24-month follow-up, an inverse probability weighting will be applied in all regression analyses to account for the differing propensity of patients with certain baseline characteristics to be included in the final analysis. All covariates included in the regression model will be included in the missingness model, including the other 5 primary endpoints. 

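### The primary renin and aldosterone models leave out baseline antihypertensive use, which is already recorded; adding it before database lock is a cheap, modest gain in precision

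*Protocol article*

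**What the plan says.** **Analysis.** The Statistical analysis plan section fits a separate linear model to each of six outcomes. Each model contains the baseline value of that biomarker, a sub-study factor, age, sex and whether the participant had seen a dietitian in the six months before baseline. No medication term is listed. Medication appears only as an example of why an extreme change might be excluded: "change in renin or aldosterone impacted by change in medications". The section also says that interactions will be tested by Wald tests in all subgroup analyses; the article does not name the subgroups.

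**Eligibility.** Table 1 requires, in both trials, "Anti-hypertensive and/or diuretic medications unchanged for three months". Both trials also exclude participants above stated diuretic doses ("Total daily diuretic therapy dose exceeding frusemide 80mg, bumetanide 2mg, hydrochlorothiazide 50mg", and further drugs) and those with "the use of both a loop and thiazide diuretic". No other antihypertensive class is restricted. One further criterion, "NSAID use for >=3 days per week (excluding aspirin <100mg/day", is an exclusion in STICK but not in COSIP.

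**Allocation.** STICK minimises on previous dietitian attendance, diabetes, hypertension and eGFR stratum. For COSIP the Randomisation section says: "In COSIP, we used computer-generated block randomization to 1:1 assign participants to intervention or usual care", and it names no balancing factor.

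**Outcomes and data.** The Study outcomes section states: "For COSTICK, the primary outcome measures are creatinine clearance, renin, aldosterone, hsTnT, proBNP and CRP". The schedule of events (Table 3) records medications at screening (T-1), at T0 and at every later visit.

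**The concern.** The plan treats medication as able to disturb renin and aldosterone, but acts on this only after randomisation, by excluding extreme changes. Baseline drug use is measured, can be fixed before allocation, and is a plausible predictor of both outcomes. It enters neither the allocation nor the models.

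Two things are at stake. First, if baseline drug use predicts the 24-month value beyond the listed covariates, leaving it out makes the confidence intervals wider than they need to be. Second, a chance imbalance in drug use between the arms stays in the estimate.

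The Introduction gives RAAS activation as one reason for doubt about low sodium intake. Readers will therefore want to know whether the effect on renin and aldosterone differs between participants who were and were not taking drugs that act on that system.

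A smaller, similar point applies to creatinine clearance. It was STICK's own primary outcome, and STICK excluded regular NSAID users. COSTICK makes it primary in COSIP participants too, and they had no NSAID exclusion.

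**Working it through.** **1. The plan's own figures.** The Sample size calculation section assumes a decline of 8 (SD 5) ml/min/1.73m² in STICK and a 25% relative reduction, so the difference is 0.25 × 8 = 2. Then n per group = 2 × (1.960 + 0.842)² × (5/2)² = 98.1, or 99 as stated. COSIP's 0.40 SD gives the same n. Its total follows as 2 × 98.1 / (0.95 × 0.85²) = 285.8, or 286 as stated. For STICK, 198/0.90 = 220 and 198/0.95² = 219.4, close to the stated 224. No sample-size figure is in dispute here.

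**2. Gain from adjustment.** Let R² be the share of residual variance that baseline drug use explains beyond the listed covariates. The documents give no value, so 2-15% is assumed.

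- The standard error is multiplied by √(1 − R²).
- Power = Φ(2.80/√(1 − R²) − 1.96), starting from 80%.
- The combined planned N is 224 + 286 = 510. The minimum detectable effect at 80% power is 2.80 × √(4/510) = 0.248 SD, multiplied by √(1 − R²).

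| R² (assumed) | Standard error lower by | Power | Detectable effect, N = 510 |
|---|---|---|---|
| 0 | 0 | 80% | 0.248 SD |
| 0.02 | 1.0% | 80.8% | 0.246 SD |
| 0.05 | 2.5% | 82.0% | 0.242 SD |
| 0.10 | 5.1% | 84.0% | 0.235 SD |
| 0.15 | 7.8% | 86.0% | 0.229 SD |

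510 is the sum of the required totals, not a count of participants enrolled.

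**3. Chance imbalance.** The 95% limit for a class with prevalence p is 1.96 × √(4p(1 − p)/N). With p assumed to be 30-50%, this is 8.0-8.7 percentage points at N = 510. If the class shifted the baseline-adjusted 24-month value by 0.5 SD (assumed), an 8.7-point imbalance would move the estimate by 0.087 × 0.5 ≈ 0.04 SD, against a detectable 0.248 SD.

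**4. Power of the interaction test.** The standard error of the difference in effect between users and non-users is that of the main effect divided by √(p(1 − p)). At p = 0.5 the factor is 2.0 and the detectable interaction is 0.248 × 2.0 = 0.50 SD. At p = 0.3 the factor is 1/√0.21 = 2.18, which gives 0.54 SD.

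**The case against.** The strongest reply is that the plan contains no error. In a randomised comparison, omitting a prognostic baseline variable neither biases the effect nor inflates the type I error, and the confidence interval already allows for chance imbalance. Each model contains the baseline value of the same biomarker, which absorbs much of a stable drug's effect. The sub-study term absorbs the average STICK-COSIP difference that follows from their different eligibility rules, and hypertension, a minimisation factor in STICK, is a partial proxy for antihypertensive use. An SAP that is not shown may already add such terms or subgroups. All of this stands, and it limits the point to a modest improvement. It does not remove the point, because the article fixes an explicit covariate list. The baseline biomarker also cannot show a different response to sodium lowering, and the sub-study term does not explain variation within COSIP.

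A reader might infer more, but the documents do not support it:

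- **That the eligibility row is wrong, or controls only recent change.** Diuretics are also limited by dose and combination in both trials, and broad drug eligibility is a legitimate design choice.
- **That drug class drives all these outcomes in everyone.** The article links only a change of medication to renin and aldosterone. It says nothing on drug class and creatinine clearance, and it does not rank RAAS activation as the main harm hypothesis.
- **That pooling users with non-users dilutes the effect.** The average over both is the intended effect in the enrolled population, and adding covariates would not change it.
- **That COSIP had no kidney screen.** COSIP excluded known CKD and a most recent eGFR of 60 or below.

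**Conclusion.** The point holds as a cheap improvement to the stated covariate list. The primary comparison is valid as written. What is given up is precision: a standard error 1-8% smaller and power of 81-86% instead of 80%, if baseline drug use explains 2-15% of the residual variance. An unlucky imbalance might shift an estimate by about 0.04 SD under the assumptions shown. Drug-class prevalence, R² and the 0.5 SD shift are all assumed. The NSAID part is weaker still, since the article does not show that frequency of NSAID use was recorded.

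The timing favours acting. The Study status section puts the trials in data cleaning, before database lock and analysis, so the terms can be added without appearing to be chosen from the results.

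**What to change.** Before database lock:

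1. Add baseline RAAS-blocker use (including mineralocorticoid antagonists), diuretic use and beta-blocker use as covariates in the renin and aldosterone models. Take them from the T-1 record, or from T0 where it precedes allocation, because the Randomisation section allows some participants to be randomised in advance of that visit. Under the plan's own rule the new terms also enter the missingness model for the inverse probability weights.
2. Name treatment by baseline RAAS-blocker use as one of the planned Wald interaction tests for renin and aldosterone. Report the effect in users and non-users, and label it exploratory.
3. For creatinine clearance, add recorded baseline NSAID use as a covariate or sensitivity analysis, if the case report form captures it.

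Do not add an analysis that applies STICK's acute kidney injury and rapid-decline exclusions to COSIP. It needs serial kidney function measurements from before entry, and Table 1 requires repeated eGFR in STICK only.

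The cost is wording in the analysis plan, coding of medications already collected, three degrees of freedom in each of the renin and aldosterone models at about 510 planned participants, and an interaction test that can detect only differences of about half an SD. If the SAP already contains these terms, a cross-reference is enough.

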**Exclusion Criteria**		
Abnormal Sodium Handling (Bartter syndrome, syndrome of inappropriate antidiuretic hormone (SIADH) secretion, diabetes insipidus or hyponatraemia (serum sodium <125mmol/L)	✓	✓
Heart Failure (New York Heart Association (NYHA) Class III or IV symptoms or known left ventricular ejection fraction 30%)	✓	✓
Total daily diuretic therapy dose exceeding frusemide 80mg, bumetanide 2mg, hydrochlorothiazide 50mg, bendroflumethiazide 2.5mg, indapamide 2.5mg, metolazone 2.5mg or the use of both a loop and thiazide diuretic)	✓	✓
Use (within one month) of tacrolimus, cyclosporine, azathioprine or mycophenolate mofetil	✓	✓
Unable to follow educational advice	✓	✓
Prescribed high-salt diet, low-salt diet or sodium bicarbonate	✓	✓
Pregnancy or lactation	✓	✓
Unlikely to comply with study procedures or follow-up visits	✓	✓
Symptomatic or treated postural hypotension	✓	✓
Known dementia or cognitive impairment	✓	✓
BMI<20 or >40kg/m ^2^	✓	✓
Participating in another clinical trial or previous study allocation	✓	✓
Acute Kidney Injury (AKI) (doubling of baseline serum creatinine within 3 months) or Rapidly declining eGFR (≥10ml/ min/1.73m ^2^) over 6 months	✓	✗
Known Kidney Disease (Post-infectious glomerulonephritis, IgA nephropathy, thin basement membrane disease, Henoch-Schonlein purpura, proliferative glomerulonephritis, membranous nephropathy (including lupus), rapidly progressive glomerulonephritis, minimal change disease or focal segmental glomerulosclerosis) or dialysis or renal transplant (prior, current or planned))	✓	✗
NSAID use for >=3 days per week (excluding aspirin <100mg/day)	✓	✗
Known CKD or most recent eGFR≤60/min/1.73m ^2^	✗	✓
Previous Cardiovascular Disease (Myocardial infarction, percutaneous coronary intervention, coronary artery bypass grafting or stroke)	✗	✓

BP=Blood Pressure; ABPM=Ambulatory Blood Pressure Monitor; FFQ=Food Frequency Questionnaire; eGFR=estimated Glomerular Filtration Rate; BMI=Body Mass Index; NSAID=non-steroidal anti-inflammatory drug; CKD=chronic kidney disease **Sodium Intake removed from Inclusion Criteria during trial due to weak correlation between dietary sodium assessment and baseline 24hour urine sodium collection

